**Supervised**			
	Logistic regression	Classification (nonlinear model)	Classification of times, “don’t knows,” and skips used by enumerator characteristics and respondent characteristics
	Linear discriminant analysis	Classification (linear model). It is a linearization of Gaussian naïve Bayes.	Classification of times, “don’t knows,” and skips used by enumerator characteristics and respondent characteristics
	Support vector machines	Support vector machines are techniques based on the calculation of the maximum margin hyperplane for classification problems.	Classification of times, “don’t knows,” and skips used by enumerator characteristics and respondent characteristics
	Classification and regression trees	A predictive model that consists of leaves that represent the target and branches that represent conjunctions of input features. Considered a subset of decision trees. Random forests operate by constructing multiple decision trees during training and aggregating their results to avoid overfitting by single trees.	Classification of times, “don’t knows,” and skips used by enumerator characteristics and respondent characteristics
	Naïve Bayes	Classification model based on probabilities.	Classification of times, “don’t knows,” and skips used by enumerator characteristics and respondent characteristics
	Neural networks	Neural networks are powerful models for machine learning. They are a generalization of linear and nonlinear models	Classification of times, “don’t knows,” and skips used by enumerator characteristics and respondent characteristics
**Unsupervised**			
	K-means	K-means clustering is a way to use data to uncover natural groupings within a heterogeneous population	Grouping of Enumerators’ times, “don’t knows,” and skips used by enumerator characteristics and respondent characteristics

#### Feedback Loops for Decision Making

Data quality issues identified during analysis will be fed back to the survey coordinator and survey team in the field. The immediate strategy for feedback will require that the data quality supervisor identifies the problem and communicates with the study coordinator via phone and email; the coordinator will then speak with the team supervisor and the enumerator (Figure 2). The study team is also exploring the possibility of automated feedback loops to capture data quality gaps identified by the machine learning algorithms and send QA issues via email or text to the study coordinators, customized calls or text alerts to team supervisors, and provide the monitoring and supervision teams with access to a web-based dashboard for data visualization (Figure 3).

Depending on the magnitude of the issue identified and its frequency, an appropriate response will be devised and may include trouble-shooting issues with CAPI/tablets, enumerator retraining or encouragement as needed, or in serious circumstances, re-interviewing the respondent. A more pervasive issue may require a team meeting where a problem with a certain question or set of the respondent population needs to be dealt with differently. Depending on the severity of the issue, the survey coordinator will be in charge of deciding how best to handle it and recheck the data to ensure the problem has been resolved.

**Figure 3 figure3:**
[figure not shown]
Automated feedback loops.

#### Outcome Assessment

Given that this is a small pilot study of this SMS feedback system, we will be assessing acceptability and feasibility. To examine if the SMS system reduces the amount of time to address errors, we will look at the difference between the date the error was made and the date it was resolved. Additionally, we plan on conducting qualitative interviews with the coordinators and supervisors to understand their perceptions of the SMS format of feeding information back and soliciting data on feasibility and acceptability. We hope to conduct in-depth interviews and focus group discussions with field staff towards the end of the data collection period to learn this information from them after they have been using the SMS system for an extended period.

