## Methods

### Survey Description

In late 2018, as part of an impact evaluation of the maternal messaging program Kilkari, a randomly selected sample of 5095 women 4-7 months pregnant, with access to a mobile phone were identified across four districts of Madhya Pradesh, India: Rewa, Rajgarh, Hoshangabad, and Mandsaur [6]. Identified women were administered a structured baseline survey tool that sought to measure their knowledge of reproductive, maternal, newborn, and child health (RMNCH) practices and observe their digital literacy. Following the baseline survey, women were randomized to receive Kilkari messages or not (status quo). In this paper, we focus on the QA procedures for the endline survey administered to women enrolled in the study at 12 months postpartum. The endline survey will be used to capture RMNCH decision making, discussion, knowledge, and practice.

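### The SMS outcome asks whether SMS reduces the time to address errors, but measures only error-to-resolution time and assigns no comparator

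*Protocol article*

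**What the plan says.** The Outcome Assessment section of the protocol article sets its scope first: "Given that this is a small pilot study of this SMS feedback system, we will be assessing acceptability and feasibility". It then states an effect question together with its measure: "To examine if the SMS system reduces the amount of time to address errors, we will look at the difference between the date". Written out, that measure is "the difference between the date the error was made and the date it was resolved". The rest of the section plans qualitative interviews and focus groups with field staff, so this interval is its only quantitative measure.

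The section Feedback Loops for Decision Making describes two routes. The one in place is personal: "The immediate strategy for feedback will require that the data quality supervisor identifies the problem and communicates with the study coordinator via phone and email". A second route is prospective: "The study team is also exploring the possibility of automated feedback loops to capture data quality gaps identified by the machine learning algorithms". For that second route the article lists email or text to coordinators, calls or text alerts to team supervisors, and a web dashboard. It gives no start date for SMS and no allocation to teams or districts. It does not say that resolution times will be compared between the two routes.

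**The concern.** A reduction is a statement about two quantities: the time to resolve errors with SMS and the time without it. The article defines one. Followed as written, the plan yields a single distribution of days, and that distribution is compatible with SMS having shortened the interval, left it unchanged or lengthened it.

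What is at stake is the conclusion the pilot may draw. The Discussion suggests that automated text and email feedback may make feedback more timely, and presents automated return of errors to the field as this study's extension of earlier work. Readers will look to this outcome for evidence. Without a planned reference, the likely fallback is an informal comparison of later errors with earlier ones. That would credit SMS with whatever field teams learned between late October 2019 and March 2020, and with the effect of any other channel that began at the same time.

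**Working it through.** The article states no sample size, effect size, standard deviation or baseline resolution time for this outcome, so there is no figure to reproduce. The check is one of reading, followed by a short illustration of precision.

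**1. Question against measure.** Let T = date resolved − date error made.
- Needed for the stated question: mean T without SMS − mean T with SMS.
- Defined in Outcome Assessment: T only.

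The word *difference* in the article refers to two dates of the same error, not to two feedback systems.

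**2. Search for a comparator elsewhere in the article.**
- *Feedback Loops for Decision Making*: phone and email are the immediate route and the automated route is being explored. This is a possible reference, but it is not assigned as one.
- *Introduction*: findings are expected on machine-learning monitoring compared with traditional monitoring. This is a general aim, with no design and no link to the SMS interval.
- *Survey Description*: women were randomised to Kilkari messages or status quo. That allocation concerns messages to women and gives no contrast between feedback routes.
- *Outcome Assessment*: field staff are to be interviewed after extended use of SMS. No non-SMS team or period is mentioned.

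No comparator is assigned to this outcome.

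**3. What an informal before/after contrast would estimate.**

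Observed change = SMS effect + change from field-team learning + effect of other channels started at the same time.

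The second and third terms enter one for one. As a hypothetical, if experience alone made resolution 2 days faster, that would read as a 2-day SMS effect. The article gives no figure for such drift.

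**4. Rough precision of a concurrent contrast between teams.** Field Coordination gives nine supervisors, each with a team, so a split would be 5 against 4. Assume m errors per team, intraclass correlation ICC, a standard deviation SD common to both groups, and 9 − 2 = 7 degrees of freedom (t = 2.365). None of m, ICC or SD comes from the article.

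Half-width of the 95% CI = 2.365 × SD × √{[1 + (m − 1) × ICC] × [1/(5m) + 1/(4m)]}

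- m = 20, ICC = 0.05: design effect 1 + 19 × 0.05 = 1.95; 1/100 + 1/80 = 0.0225; √(1.95 × 0.0225) = 0.209; half-width 2.365 × 0.209 = 0.50 SD.
- m = 40, ICC = 0.01: √(1.39 × 0.01125) = 0.125; half-width 0.30 SD.
- m = 10, ICC = 0.10: √(1.90 × 0.045) = 0.292; half-width 0.69 SD.

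| Assumed SD | Central case | Range over m = 10–40, ICC = 0.01–0.10 |
|---|---|---|
| 3 days | ±1.5 days | ±0.9 to ±2.1 days |
| 6 days | ±3.0 days | ±1.8 to ±4.1 days |

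The half-width scales directly with the SD, so these figures are only a guide. They also treat the nine teams as independent, which is optimistic because only two coordinators serve them.

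**The case against.** The strongest reply rests on scope. The section calls itself a small pilot of acceptability and feasibility, and the automated loop is still under exploration. Time to resolution is then a secondary look inside a feasibility exercise. This stands, and it limits the severity.

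A second reply is that the two routes, read together, imply a reference: *reduces* means by comparison with phone and email. The interval could be computed for errors handled by either route if the dates are kept. This also stands in part. A reader might infer that no result could ever show a reduction, whatever the sample size. The article does not support that. It leaves the comparator unassigned and does not rule one out.

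A third reply is that a journal article condenses, and the choice of reference period or teams may sit in a fuller document. That would answer a complaint about missing detail. It does not answer this point, because the article gives the question and the measure in one sentence and the two do not match.

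Finally, a reader might infer that the listed channels will be switched on together, so that SMS could never be separated from them. The article lists options and does not say when any of them starts. Simultaneous start is a risk to record, not a stated feature of the plan.

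**Conclusion.** The point holds as a mismatch between question and measure. With no comparator assigned, the stated analysis cannot support a conclusion that SMS reduces time to address errors. This follows from the text and needs no numerical assumption.

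The issue is moderate. It affects one outcome of the SMS pilot. A reader might take it as a threat to the Kilkari impact evaluation, but the randomisation there concerns messages to women, and its endpoints do not depend on the feedback route. Nor does the point oblige the study to add a randomised comparison of feedback routes. A descriptive outcome would fit the declared feasibility aim. The precision figures are illustrative and rest wholly on assumed values.

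**What to change.** Choose one of two courses and state it in Outcome Assessment.

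**If a reduction is to be examined.** Name the phone and email route as the reference. Log the error date and the resolution date for issues handled by that route as well as by SMS. Compare the intervals for the same error types, with supervisor team as the cluster, and report the difference with its confidence interval. State that a before/after contrast is confounded by field-team learning and by any other channel started at the same time.

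A staggered start of supervisor alerts by team would allow comparison within the same calendar weeks and reduce the confounding by learning. It is optional: the field period is short, the SMS start is not given, and practice may spill over between teams through the two shared coordinators.

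**If no reference is logged.** Reword the aim as *to describe the time to resolution under the SMS system*, and draw no conclusion on reduction.

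The first course costs some extra date logging and one further analysis, and the interval may be wide. The second costs only a change of wording and a weaker claim.

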Data analytics is an increasingly vital part of survey QA, particularly in light of the increasing use of tablets and other electronic tools which enable rapid, if not real-time, data access. Routine data analytics are most often concerned with outlier analyses that monitor a series of data quality indicators, including response rates, missing data, and reliability of coefficients for test-retest interviews. Dashboards may be used to visualize key tracking indicators and provide a snap-shot of survey implementation status. Collectively, while these procedures help ensure basic data quality, they fall short of optimizing the full potential of rapid data access borne from the use of electronic tools during survey implementation.

Machine learning is emerging as a tool with the potential to enhance real-time data monitoring by identifying trends in data collection that could compromise quality [3]. Machine learning covers a broad array of computationally-intensive methods aimed at detecting patterns in the data, including outliers and subtle trends that would not always be noticed via manual data cleaning and analysis. In the context of QA for survey monitoring, machine learning can be used to classify the data by the severity of outliers using either supervised techniques—with labeled training or pilot data—or a variety of unsupervised techniques [4].

Household surveys are expensive, time-consuming, and resource-intensive. Recognizing this, to date, applications of machine learning as part of household surveys have sought to reduce the expense of surveys by using satellite or phone data to predict socioeconomic distribution in a country [5]. However, little work has been done using machine learning techniques to improve the monitoring of surveys. To address this gap, we aim to outline a comprehensive strategy for monitoring the quality of data emerging from a large population-based household survey in rural India, including the use of machine learning techniques. Study findings are anticipated to shed light on the feasibility and effectiveness of advanced monitoring using machine learning as compared to traditional monitoring techniques.

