#### Field Monitoring

Field monitoring consists of both confirming the eligibility of respondents as well as spot checks. Both these aspects happen at each of the five levels of field hierarchy: (1) enumerator, (2) immediate field supervisor, (3) coordinator, (4) field-level data quality supervisor, and (5) back-end data quality supervisor. At the enumerator level, any issues or red flags identified by enumerators will be reported back to their immediate supervisor who assigned them to the interview; these could include issues of eligibility or issues with tablets or other interview processes. Immediate field supervisors will focus principally on locating respondents and monitoring interviews. The former occurs based on the respondents the field coordinators give each supervisor—the respondent is located, and eligibility is confirmed. Then the supervisor may monitor part or all of the interview either through spot-check observation or form check and keep track of completion or any needed follow-up visits. The coordinators will manage larger village/block level logistics to ensure all eligible participants in an area have at least been visited once on a trip and also complete random spot-checks as their logistics duties allow. The field level quality supervisor will complete spot-checks as well as follows-up on any systemic issues found in both eligibility checking or back-end data monitoring either by individually speaking with enumerators/supervisors or discussing any data quality issues during debriefing meetings with the team. Finally, the back-end data quality supervisor will check weekly data uploads for any entry errors relating to eligibility, such as incompatible birth age or incorrect unique identifier. They will also assess mechanistic indicators such as time to interview completion or rate of skips or “don’t know” responses that warrant further observation of participating enumerators. The larger research team will conduct monthly checks on the field teams.

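### The outcome assessment asks whether SMS feedback shortens the time to fix errors, but its only measure is an interval with no non-SMS reference

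*Protocol article*

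**What the plan says.** The Outcome Assessment section opens with a limited scope: "Given that this is a small pilot study of this SMS feedback system, we will be assessing acceptability and feasibility". The next sentence sets a comparative question, "To examine if the SMS system reduces the amount of time to address errors", and names one measure for it: "we will look at the difference between the date the error was made and the date it was resolved". Field staff are to be interviewed late in data collection, "after they have been using the SMS system for an extended period".

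The section on feedback loops describes the current route. The data quality supervisor finds a problem and "communicates with the study coordinator via phone and email", after which the coordinator speaks to the team. The automated route has a tentative status: "The study team is also exploring the possibility of automated feedback loops". On detection, the Field Monitoring section says that "the back-end data quality supervisor will check weekly data uploads" for eligibility-related entry errors.

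On machine learning, the Introduction expects findings to throw light on the "feasibility and effectiveness of advanced monitoring using machine learning as compared to traditional monitoring techniques".

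**The concern.** The question and the measure do not match. Whether something is reduced can be judged only against what happens without it, and the plan measures only what happens with it. This is more than a detail left to a fuller document, because the article states the question and also fixes the measure meant to answer it. No later choice of summary statistic or model can add the missing reference.

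Timing matters too. The comparator depends on which errors, teams or weeks go by which route and on what the error log records. According to the abstract, fieldwork runs from late October 2019 to March 2020. A reference that is not set up during that time may not be recoverable. The pilot could then report a resolution time that readers take as evidence of faster correction when it is not.

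**Working it through.** The article gives no sample size, power, significance level or effect size for the SMS or machine-learning evaluation, so there is no figure to reproduce. The 5095 women are the survey sample, not a sample size for this question. The check is one of reading, with one illustration.

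**Step 1: is the contrast defined?** Let R = T(without SMS) − T(with SMS), where T is mean or median time to resolution.
- T(with SMS): supplied by the error-to-resolution interval in Outcome Assessment.
- T(without SMS): Outcome Assessment names no earlier period, no non-SMS teams and no phone or email reference. The feedback section describes both routes but does not set one against the other. It gives the automated route no start date, phasing or allocation. The only randomization (Survey Description) assigns women to Kilkari messages or status quo, not errors or teams to a feedback route.

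One of the two terms is therefore missing. If the observed value were 4.0 days (hypothetical), R would be 1.5 days if the reference were 5.5, zero if it were 4.0, and negative if it were lower. The planned data cannot tell these apart.

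**Step 2: what does the interval contain?** Write T = L + D, where L is error to detection and D is detection to resolution. A message can act on D. It changes L only if detection itself is also speeded up. All figures below are assumptions.
- If the weekly review governs detection and errors fall evenly over the week, L runs from 0 to 7 days, with mean 7/2 = 3.5 and SD 7/√12 = 2.02.
- Suppose SMS cuts D from 2.0 to 0.5 days: (2.0 − 0.5)/2.0 = 75%.
- T then moves from 3.5 + 2.0 = 5.5 to 3.5 + 0.5 = 4.0 days: 1.5/5.5 = 27%.
- Range: with mean L = 0, T goes from 2.0 to 0.5 (75%). With mean L = 7, it goes from 9.0 to 7.5 (1.5/9.0 = 17%).

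The same cut in D thus shows as anything from 17% to 75% of the planned measure, depending on a lag that the plan does not ask to be recorded separately.

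**Step 3: machine learning against traditional monitoring.** The model-building step compares algorithms with one another and tests them on withheld data labeled true or false. Outcome Assessment deals with SMS only. Neither compares machine-learning flags with those of the back-end supervisor, so the contrast expected in the Introduction has no analysis behind it.

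**The case against.** The strongest reply is the declared scope. This is a small pilot of acceptability and feasibility, and a single-group design with staff interviews serves those aims well. That stands, and it lowers the severity. It does not answer the comparative question posed in the very next sentence.

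A second reply is that the article does not rule out a before/after reference, since phone and email are the immediate route and automation is still being explored. That is true, and it makes the fix easy. But a comparison that is possible has not thereby been planned.

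Some stronger readings are tempting, and the article does not support them:
- *Machine learning against traditional monitoring is the main claim and rests on no data.* The abstract's objective is to describe methods that use both, and the Discussion presents machine learning as a complement to traditional checks. The comparative phrase is an expectation in the Introduction, not an outcome or hypothesis.
- *Unresolved errors are dropped, which flatters SMS.* They have no resolution date, and the article gives no rule for them, but nothing says that they are excluded. Such a rule commonly sits in an analysis plan.
- *The clock starts in the wrong place.* Flagging and relay can be seen as one system whose purpose is timely correction while teams are still in the area. For that purpose, error to resolution is a defensible end-to-end measure.
- *Automated alerts must wait up to a week.* The weekly cycle is described for the back-end supervisor. The article does not say that automated alerts follow it.

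**Conclusion.** The concern holds for the SMS question. As written, the plan can describe time to resolution under SMS but cannot show that SMS reduces it. This conclusion rests on the text alone and needs no numerical assumption. The figures of 27% and 17% to 75% only illustrate why detection should be dated separately, and they depend on assumed lags and fix times.

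The machine-learning point is secondary: a soft comparative expectation that no planned analysis meets.

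Severity is moderate. The declared pilot aims are unaffected, and so is the randomized comparison of Kilkari messages described in the article. What cannot be supported is a conclusion about reduction, or about machine learning relative to traditional monitoring.

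**What to change.** 1. **Name a comparator.** Compare with errors handled by phone and email, using either the period before SMS starts or a staggered start across the 9 supervisor teams. Assigning individual errors to a route at random is less attractive, because the same 2 coordinators and 9 supervisors would work with both routes at once.
2. **Log four dates and the route.** For each error, record when it was made, detected, alerted and resolved, and which route carried it. Record also how it was found, since the automated loop is meant to carry algorithm-identified gaps and a difference in error type could pass for a difference in route.
3. **Report two intervals.** Give error to resolution and detection to resolution together. Keep unresolved errors in the analysis, censored at the end of fieldwork, for example with a Kaplan-Meier median.
4. **If no comparator is possible,** replace the question about reduction with a description of time to resolution under SMS.
5. **Machine learning.** Either compare machine-learning flags with the back-end supervisor's rule-based flags against discordance in the 10% recheck (sensitivity, positive predictive value), or drop the comparative wording in the Introduction. In the first case the models must be built without the resample indicator. Table 1 lists it among the machine-learning indicators, and Data Analytics lists the recheck survey as a data source, so the check would otherwise be circular.

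The cost is a few columns in the error log and a small analysis. Some teams or weeks stay on phone and email for longer. A contrast across 9 teams is imprecise, and one between periods is open to time trends such as growing enumerator experience, so the result should be reported as exploratory.
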